## Abstract

**Background:**

Manipulation is a common treatment for non-specific neck pain. Neck manipulation, unlike gentler forms of manual therapy such as mobilisation, is associated with a small risk of serious neurovascular injury and can result in stroke or death. It is thought however, that neck manipulation provides better results than mobilisation where clinically indicated. There is long standing and vigorous debate both within and between the professions that use neck manipulation as well as the wider scientific community as to whether neck manipulation potentially does more harm than good. The primary aim of this study is to determine whether neck manipulation provides more rapid resolution of an episode of neck pain than mobilisation.

**Methods/Design:**

182 participants with acute and sub-acute neck pain will be recruited from physiotherapy, chiropractic and osteopathy practices in Sydney, Australia. Participants will be randomly allocated to treatment with either manipulation or mobilisation. Randomisation will occur after the treating practitioner decides that manipulation is an appropriate treatment for the individual participant. Both groups will receive at least 4 treatments over 2 weeks. The primary outcome is number of days taken to recover from the episode of neck pain. Cox regression will be used to compare survival curves for time to recovery for the manipulation and mobilisation treatment groups.

**Discussion:**

This paper presents the rationale and design of a randomised controlled trial to compare the effectiveness of neck manipulation and neck mobilisation for acute and subacute neck pain.

## Background

Manual techniques are routinely used in the management of non-specific neck pain and appear to provide effective pain relief for at least some neck conditions [1-5]. These techniques include manipulation, a high velocity thrust directed at the joints of the spine, and mobilisation techniques that do not involve a high velocity thrust. Manipulation is associated with a small risk of serious cerebrovascular injury [6,7], whereas mobilisation is generally considered to be a safer technique [8]. However in clinical situations where manipulation is indicated it is thought to provide better results than mobilisation.

Both manipulation and mobilisation are more effective in relieving chronic neck pain than general practitioner care [3,9] or no treatment controls[2]. Few trials have investigated manual therapy for acute neck pain [1] or compared the effectiveness of manipulation and mobilisation[2]. There is some evidence that a single manipulation provides greater improvement in neck pain and range of motion, than mobilisation when these outcomes are measured immediately following a treatment [10,11]. It is not known however, if manipulation leads to more rapid or more complete recovery from an episode of recent onset neck pain than safer manual therapy techniques.

Neck manipulation is an independent risk factor for vertebrobasilar stroke in young adults [6,12]. The proposed mechanism of injury is dissection of the intima or media lamina of the vertebral artery [13]. Compromise of vertebrobasilar circulation can result in mild transient symptoms such as dizziness or loss of balance, or in more serious cases "locked in" syndrome, Wallenberg syndrome or death [7,14,15]. Estimates of incidence of serious complications from neck manipulation are imprecise, ranging between 1 serious complication for every 1,000,000 treatments [16,17] and 1 for every 10,000 treatments [18]. It is generally accepted that the risks might be higher [14,17,19,20] because there are no mandatory reporting requirements or standard systems for reporting manipulation accidents. Although cerebrovascular complications from neck mobilisation have been reported, these are mostly of a transient and minor nature [21,22]. The only exception is one recorded case of stroke, following vigorous rotation mobilisation [22].

There is long standing and vigorous debate both within and between the professions that use neck manipulation as well as the wider medical community as to whether neck manipulation does more harm than good[23]. Manipulation has potential benefits that include hastening of recovery of symptoms and restoration of normal function in the early stages of an episode of neck pain. We will conduct a randomised controlled trial to determine whether neck manipulation provides faster resolution of symptoms than mobilisation in patients with an episode of acute or subacute non-specific neck pain. It is hypothesised that an acute episode of neck pain will resolve more rapidly when treated with manipulation than with mobilisation.

## Methods/Design

A randomised controlled trial with two treatment arms will be conducted at private physiotherapy, chiropractic and osteopathic clinics in Sydney, Australia. Participants with neck pain of recent onset will be randomised to receive treatment with either manipulation or mobilisation. Randomisation will occur at the treatment session at which the treating practitioner decides that manipulation is an appropriate treatment. Ethics approval has been granted by The University of Sydney Human Research Ethics Committee. Consent will be obtained from each participant prior to entry into the trial.

### Study Sample

One hundred and eighty-two participants will be recruited from among patients presenting for physiotherapy, chiropractic or osteopathic treatment of acute or subacute neck pain. Patients who satisfy the inclusion criteria will be invited to participate in the study.

### Inclusion criteria

The aim of this trial is to establish the effectiveness of manipulation compared with mobilisation for conditions that are treated with manipulation in contemporary practice and are likely to benefit from manipulation. For this reason participants are only eligible for inclusion in the trial if the treating practitioner decides that manipulation would be an appropriate treatment for the individual patient. Patients for whom manipulation is thought not to be indicated will be excluded by the practitioner. In these cases the practitioner is asked to provide a reason why they consider manipulation to be inappropriate in the circumstances.

Participants entering the trial must be aged between 18 and 70 years and have a primary complaint of non-specific neck pain that is located at least partly in the area defined by Merskey [24]

*anywhere within the region bounded superiorly by the superior nuchal line, inferiorly by an imaginary line through the tip of the first thoracic spinous process and laterally by sagittal planes tangential to the lateral borders of the neck*. p 11

The episode of neck pain must be of less than 3 months duration and preceded by at least one month without neck pain. The pain must be of sufficient intensity (greater than 2 out of 10 on a numerical pain scale) to permit a clinically worthwhile effect to be demonstrated.

### Exclusion criteria

Participants will be excluded if their neck symptoms are related to a motor vehicle accident or significant trauma; if their condition involves predominantly arm symptoms; if there are signs of serious pathology such as malignancy, infection, inflammatory disorder or fracture; if there are signs of cervical spinal cord compromise (determined by the presence of any of the following signs; diffuse sensory abnormality, diffuse weakness, hyperreflexia or presence of clonus) or radiculopathy (determined by the presence of 2 of the following signs; dermatomal sensory abnormality, myotomal weakness or diminished/absent tendon jerk reflexes) or if they have undergone neck surgery in the previous 12 months.

A record will be kept of the number of subjects excluded from the study as well as those who are eligible for inclusion and choose not to participate. Reasons for not participating will be sought.

### Baseline measurements

Baseline data will be collected at the initial appointment about the demographic and clinical characteristics of participants. Socio-demographic data will be collected using items from the Australian Census 2001 [25] and using standard classification of employment [26] and education status [27]

We will collect measures of pain [28] (average pain over the last 24 hours rated on a 0–10 numerical rating scale) neck-related disability [29], patient-specific disability [30] and quality of life [31] when patients first present for treatment. The pain, disability and quality of life measures will be assessed again immediately prior to randomisation as baseline outcome measures for the trial.

### Treatment allocation

Current neck manipulation guidelines recommend that initial treatments be conservative and the effects of treatment carefully monitored prior to treatment with neck manipulation [8]. Participants will be randomised to a treatment group only after the treating practitioner has established that neck manipulation is the treatment of choice in the circumstances. Late randomisation is a feature of good trial design [32] and in this case will ensure that the trial reflects current clinical practice. In the period prior to randomisation participants will receive treatment that is consistent with evidence-based guidelines for the treatment of acute neck pain [33].

A statistician who is not involved in subject recruitment or data collection will produce consecutively numbered sealed opaque envelopes containing the treatment allocation for each patient. The randomisation sequence will contain equal numbers of subjects in each group but will be otherwise unrestricted.

### Interventions

Assessment and treatment will be conducted by experienced manipulative physiotherapists, chiropractors and osteopaths. Participating physiotherapists will have postgraduate university qualifications in manipulative physiotherapy and at least 2 years post graduate experience. Participating chiropractors and osteopaths will have a university chiropractic or osteopathic degree and at least 2 years of clinical experience.

Participants will be allocated to one of two treatment arms.

*Manipulation Group: *a course of manual treatment consisting of high velocity, low amplitude movements applied to the cervical spine by the therapist. Participants will receive at least 4 treatments over 2 weeks.

*Mobilisation Group: *a course of manual treatment consisting of low velocity oscillatory movements applied to the cervical sine by the therapist. Participants will receive at least 4 treatments over 2 weeks.

Treatment may be discontinued prior to the fourth treatment, in either of the treatment arms if the participant completely recovers or if they experience a serious adverse response to treatment. Within these guidelines the number and type of manipulation and mobilisation techniques will be determined by the practitioner. The type of manipulative or mobilising technique will not be standardised, as this might result in inappropriate treatment for some patients. The practitioner will keep a record of the number and type of techniques used. The intervention period will be up to 2 weeks.

Clinical practice guidelines recommend that manipulation and mobilisation be used as part of a multimodal management strategy incorporating other effective treatments rather than as stand-alone techniques [34]. All participants may therefore receive other evidence-based treatments including advice, reassurance, encouragement to resume usual activities, and will be asked to continue with any exercise regimen that they had previously commenced. The use of manipulation or mobilisation of the thoracic or lumbar regions of the spine will not be constrained in either group. Treatment with a combination of neck manipulation and mobilisation techniques, as sometimes occurs in clinical practice will not be permitted for either group.

During the intervention period both groups will be asked to refrain from seeking other treatment but will be permitted to continue pain medication. Participants will be asked to keep a record of any additional treatment received, the type of treatment, the date of this treatment and its effects. Participants will not be discouraged from seeking further treatment at the conclusion of the 2-week trial period, but will be asked to keep a record of any further treatment received as for the trial period.

### Outcome measures

#### Primary outcome

Outcome measures will be recorded by a researcher who is blinded to subject allocation. The primary outcome measure is the number of days taken to recover from neck pain. Participants will be considered to have recovered when they rate pain intensity as <1/10 for more than 7 consecutive days. For the purposes of analysis the recovery will be determined as the first of those 7 days.

Participants will be asked to keep diaries of pain intensity. They will record average pain over each 24 hour period on a 0–10 scale. Participants will be asked to complete this record on a daily basis for the first 4 weeks, then weekly for the next 4 weeks. Participants will be contacted by telephone on a weekly basis for the first 4 weeks to encourage them to complete their diaries and to collect diary data. Pain scores for the next 2 months will be collected by telephone at monthly intervals.

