### Sample size calculations

The sample size of 182 participants gives an 80% probability of detecting a reduction in median survival time from 21 to 12 days, or equivalently from 35 to 20 days assuming alpha = 0.05.

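### Recovery requires a run of more than 7 daily scores, but daily scoring stops at week 4, so the primary definition cannot be applied to recoveries starting after day 21

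*Protocol article*

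**What the plan says.** In the protocol article, Primary outcome, the endpoint is a time in days: "The primary outcome measure is the number of days taken to recover from neck pain". The event is defined by a run of scores: "Participants will be considered to have recovered when they rate pain intensity as <1/10 for more than 7 consecutive days". The next sentence dates it: "For the purposes of analysis the recovery will be determined as the first of those 7 days".

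Each score covers a single day: "They will record average pain over each 24 hour period on a 0–10 scale". Participants are asked to "complete this record on a daily basis for the first 4 weeks, then weekly for the next 4 weeks". After the weekly calls of the first 4 weeks, "Pain scores for the next 2 months will be collected by telephone at monthly intervals".

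Under Sample size calculations, 182 participants are said to give 80% power at alpha 0.05 for "a reduction in median survival time from 21 to 12 days, or equivalently from 35 to 20 days". Under Data analysis, the groups are compared by Cox regression on time to recovery.

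**The concern.** The event definition and the collection schedule do not fit together. The definition needs scores on consecutive days. From week 5 the schedule no longer scores any two consecutive days, so a single weekly or monthly score cannot show that a participant met the definition or on which day the run began.

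This is more than a detail that an article might leave to a fuller document. Both the definition and the schedule are stated here, and a later analysis plan cannot recover daily scores that were never collected.

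The trial's question is how fast patients recover, and one of its two planning scenarios puts the control median two weeks past the last start day that the diary can confirm. At stake are the number of usable events in that scenario, whether its control median can be estimated, and the claim that the two scenarios are equivalent. The two sentences of the definition also disagree on the length of the run.

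**Working it through.** **Inputs from the article.** N = 182; equal allocation, so 91 per arm; alpha 0.05; medians 21 vs 12 or 35 vs 20 days; daily scores for 4 weeks, taken as days 1 to 28.

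**Assumptions not in the article.** Exponential recovery times, no dropout, a two-sided test, and follow-up of 84 days.

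**1. The plan's own figure.** Both scenarios have the same ratio: 12/21 = 20/35 = 0.571, a recovery hazard ratio of 1.75. The article does not give its method. Comparing the proportions recovered at the control median, 1 − 0.5^(21/21) = 0.500 vs 1 − 0.5^(21/12) = 0.703, gives 91 per arm, or 182 in total, for 80% power. The 35 vs 20 scenario gives the same proportions, and so the same N, when read at day 35. Freedman's formula needs 106 events. Divided by the mean event probability at day 21 (0.601), that gives N = 177, within 3% of 182. So the stated N reproduces with a horizon near the control median.

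**2. Last confirmable start day.** A run of k daily scores inside days 1 to 28 must start by day 28 − k + 1.
- More than 7 days (k = 8): day 21.
- 7 days (k = 7): day 22.

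**3. Confirmable recoveries.** P(recovered by t) = 1 − 0.5^(t/median).

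| Medians (days) | Control by day 21 | Manipulation by day 21 | Events by day 21 | Events by day 84 | Share confirmable |
|---|---|---|---|---|---|
| 21 vs 12 | 0.500 | 0.703 | 91 × 1.203 = 109.4 | 175.6 | 62% |
| 35 vs 20 | 0.340 | 0.517 | 91 × 0.857 = 78.0 | 159.8 | 49% |

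**4. Power on confirmable recoveries.** Power = Φ(√d/2 × ln 1.75 − 1.96), with ln 1.75 = 0.560.
- 21 vs 12: √109.4/2 × 0.560 − 1.96 = 0.97, so power is 83%.
- 35 vs 20: √78.0/2 × 0.560 − 1.96 = 0.51, so power is 69.5%.
- 35 vs 20 with the limit at day 22: 80.7 events, 71%.

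For 80% power at 35 vs 20 days with the day-21 limit, N would be about 236 (Schoenfeld, 101 events) or 248 (Freedman, 106 events).

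**5. Sensitivity to sidedness.** The article does not say whether alpha is one- or two-sided. One-sided at 0.05, the 35 vs 20 power with the day-21 limit would be 79.6%. The exact reproduction of 182 in step 1 is two-sided.

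**6. Control median.** With 34% of controls confirmable by day 21, the control curve does not reach 50% in the 35 vs 20 scenario. This does not depend on sidedness.

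**The case against.** The best defence has three parts, and much of it stands.

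First, the sample size is not shown to be wrong. It reproduces, and in the first-named scenario power stays at about 83% on confirmable recoveries alone. A reader might infer that the trial is underpowered throughout; the figures do not support that. Nor does censoring everyone at day 21 by itself bias the hazard ratio under proportional hazards. It costs events, and in the slower scenario it costs the control median.

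Second, the later scores are not worthless. Weekly and monthly readings can bracket a late recovery, and a full protocol or analysis plan might say how. That stands as far as it goes, but a bracket does not satisfy a definition built on consecutive days.

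Third, the article does not say what will happen to late recoveries. A reader might infer that single late scores will count as recovery, that their dates will be treated as exact, and that the hazard ratio will therefore be pulled towards 1. The article states none of these rules. All that can be said is conditional: if single late scores were accepted, the event definition would change during follow-up, and dates would be known only to within 1 to 4 weeks.

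A reader might also object to counting days 22 to 28 as time at risk. That does not change the Cox estimate for participants followed to day 28, because the partial likelihood changes only at event times.

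The mismatch over 7 days is a small slip: it moves the limit by one day.

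**Conclusion.** The concern holds in a limited form. As written, the primary definition can be applied only to recoveries starting by day 21, or day 22 on the shorter reading, and the article does not say how later ones are handled.

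For 21 vs 12 days, the stated 80% power survives (about 83%). For 35 vs 20 days, about 78 of 160 expected recoveries are confirmable, power is about 70%, and the control median cannot be estimated. Under this schedule the two scenarios are not equivalent.

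The event counts rest on exponential recovery and no dropout. The power figures also assume a two-sided test; a one-sided test would bring the second scenario to about 80%. The limit on the start day, and the position of a 35-day control median beyond it, need none of these assumptions. The mismatch should be settled before data collection, because missing daily scores cannot be supplied afterwards.

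**What to change.** Choose one of the following and state it in the Primary outcome section.

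- **Extend the diary.** Continue daily pain scores beyond week 4, up to week 12, for participants who have not completed a qualifying run. With daily scores to day 84, an 8-day run can start as late as day 77. For 35 vs 20 days that gives 91 × (0.782 + 0.931) = 155.9 events and power of about 94% on the same assumptions. The cost is extra diary days for unrecovered participants, with monitoring then depending on recovery status.
- **Ask at the later contacts.** At each planned contact, ask when pain first fell below 1/10 and whether it stayed there for the required run. Analyse recoveries after the daily-diary window as interval-censored. The cost is an added question and some recall error in the dates.
- **If collection cannot change.** Declare the primary analysis censored at the last confirmable start day, and restate power for 35 vs 20 days as about 70% (two-sided). The cost is that a 35-day control median will not be estimated.

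In every case, use one run length in both sentences of the definition. The first two options need a protocol amendment, and the first also a diary amendment.

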#### Secondary outcomes

The time to recovery from neck-related disability will be measured using a single item disability scale modified from the MOS-SF36 survey [35]. Participants will record in their diary the degree to which neck pain interfered with normal daily activities on a 5 point scale with responses ranging from "did not interfere at all" to "interfered extremely" with daily activities. Recovery is defined as a rating of "did not interfere at all" on this scale. Participants will be contacted by telephone on a weekly basis for the first 4 weeks to monitor compliance with completing the diary and to collect diary data. Disability scores will be collected by telephone at monthly intervals for the next 2 months.

A neck-specific measure of disability [29] and a patient-specific measure of disability [30] will be completed at the 4 week and 12 week phone interview. Global perceived effect of treatment [36] will be recorded at the 2 week and 12 week phone interview. Participants will be questioned at the 12 week phone interview about the frequency and duration of neck pain after recovery to determine the incidence of recurrent and new episodes of neck pain. As there are no accepted definitions of recurrence of an episode of neck pain, definitions proposed for recurrent episodes of low back pain will be used [37]. A new episode of neck pain is defined as an episode of neck pain lasting at least 24 hours preceded by at least one month without neck pain. A recurrence is defined as pain of at least 24 hours duration within one month of recovery. A record will be kept of the number of days lost from work due to neck pain over the 3-month period [36].

The participants' perception of the treatment credibility [38] will be recorded in the participant diary after the first treatment. The number and type of treatments provided in the period between the initial physiotherapy or chiropractic appointment and randomisation will be recorded by the practitioner after randomisation.

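### Recovery from disability is met by one no-interference rating, while recovery from pain needs more than 7 consecutive days, so the secondary outcome times the first good rating

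*Protocol article*

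**What the plan says.** All references are to the protocol article.

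- **Secondary outcomes, type of outcome.** It is a time to event: "The time to recovery from neck-related disability will be measured using a single item disability scale modified from the MOS-SF36 survey".
- **Secondary outcomes, event.** "Recovery is defined as a rating of 'did not interfere at all' on this scale". No number of days, confirming rating or dating rule follows.
- **Secondary outcomes, collection.** "Participants will record in their diary the degree to which neck pain interfered with normal daily activities on a 5 point scale". No frequency is given for this item. Diary data are collected by weekly telephone calls for 4 weeks, and disability scores by monthly calls for the 2 months after that.
- **Primary outcome, event and date.** "Participants will be considered to have recovered when they rate pain intensity as <1/10 for more than 7 consecutive days", and "For the purposes of analysis the recovery will be determined as the first of those 7 days". The pain record is explicitly daily for the first 4 weeks.
- **Inclusion criteria.** "The pain must be of sufficient intensity (greater than 2 out of 10 on a numerical pain scale"; there is no matching minimum for interference or disability.
- **Baseline measurements.** "The pain, disability and quality of life measures will be assessed again immediately prior to randomisation as baseline outcome measures for the trial". The disability measures named there are the neck-specific and patient-specific ones (references 29 and 30). The single interference item (reference 35) is not listed.

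**The concern.** The two recovery outcomes share a name and, as far as one can tell, a diary, but they rest on different kinds of event. Pain recovery is a sustained state. Disability recovery is reached at the first rating in the lowest of five categories and cannot be undone. This has three consequences:

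1. An isolated good rating, such as a rest day, counts as recovery.
2. Pain and disability recovery times cannot be set side by side, because a participant can be recovered on one while far from the criterion on the other.
3. A participant who enters with pain above 2/10 but no interference is recovered at the first rating and carries no information on speed of recovery.

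At stake is the meaning of the trial's only time-to-event measure of disability. This is not a detail left to an analysis plan, because the article states the event rule in full and, in the section just before, gives pain both a duration and a dating rule.

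**Working it through.** The article gives no figure for disability recovery, so there is none to reproduce. The check has two parts.

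**Side-by-side reading**

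| Element | Pain (primary) | Disability (secondary) |
|---|---|---|
| Threshold | below 1/10 | lowest of 5 categories |
| Duration | more than 7 consecutive days | none; one rating |
| Date of event | first day of the run | not stated |
| Minimum at entry | above 2/10 | none |
| Rating frequency, weeks 1 to 4 | daily | not stated (diary) |
| Telephone scores in the following 2 months | monthly | monthly |

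Nothing in the Secondary outcomes section carries the pain rule over to disability.

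**Illustration of what the rule admits**

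Take a participant whose interference fluctuates with no real trend. Let q be the chance that any one rating falls in the no-interference category. The values of q are assumed, and ratings are taken as independent with constant q.

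Single-rating rule: P(counted as recovered within k ratings) = 1 − (1 − q)^k.

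- q = 0.05: k = 7 gives 1 − 0.95^7 = 30%; k = 14 gives 51%; k = 28 gives 76%.
- q = 0.10: 52%, 77% and 95%.
- q = 0.20: 79%, 96% and 99.8%.

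The median day of such a recovery is the smallest k with 1 − (1 − q)^k ≥ 0.5: day 14, day 7 and day 4 respectively.

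Sustained rule: more than 7 consecutive daily ratings means 8 in a row. The exact probability of at least one such run in 28 independent ratings comes from stepping day by day through the current run length:

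| q | Single rating, 28 days | Run of 8, 28 days |
|---|---|---|
| 0.05 | 76% | <0.1% |
| 0.10 | 95% | <0.1% |
| 0.20 | 99.8% | <0.1% |
| 0.30 | about 100% | 0.1% |
| 0.50 | about 100% | 4.3% |
| 0.70 | about 100% | 37.2% |

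The pain dating sentence speaks of 7 days rather than more than 7. With a run of 7 the figures at q = 0.30, 0.50 and 0.70 are 0.3%, 8.8% and 51.9%. The contrast with the single-rating rule is large up to q = 0.50 and narrows at 0.70.

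**Sensitivity to rating frequency.** If the item were rated weekly, there would be about 4 ratings in weeks 1 to 4, and 1 − (1 − q)^4 gives 19% (1 − 0.8145), 34% (1 − 0.6561) and 59% (1 − 0.4096) for q = 0.05, 0.10 and 0.20. These are smaller but not trivial. At that frequency a consecutive-day rule could not be applied at all.

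**Limit on a sustained rule.** With daily ratings to day 28, a run of 8 can be confirmed only if it starts by day 21 (days 21 to 28). Monthly calls cannot confirm one afterwards.

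**The case against.** The case against is strong on size and remedy, and weaker on the defect itself.

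- **Daily rating is inferred.** A reader might assume 28 daily chances to meet the rule. The explicit daily schedule belongs to the pain record; for interference, only the diary is mentioned. This stands, and the daily figures are conditional on it.
- **Independence is assumed.** Interference within one episode is probably correlated from day to day. Positive correlation lowers the single-rating probabilities and raises those for runs, so the gap between the rules shrinks. This stands.
- **Dilution is not shown.** A reader might infer that the rule must mask a treatment difference. The article does not support that: if one treatment yields more good days, times to the first good day would differ too. Blurring is likely, but not demonstrated.
- **Starting without interference may be rare.** Participants are seeking treatment for neck pain above 2/10, and the article does not say how many report no interference. The rule allows the case; its frequency is unknown.
- **Excluding on the first diary rating would bias the comparison.** Because the single item is not listed among the pre-randomisation measures, it is tempting to use the first diary entry instead. Randomisation takes place at a treatment session, so that entry may follow allocation and the first treatment. Dropping participants on it could remove immediate responders, unequally by arm, and would depart from the intention-to-treat principle in Data analysis. This stands in full.
- **The consequence is limited.** This is one secondary outcome, and disability is also measured on two other scales at 4 and 12 weeks. This too stands.

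None of these points supplies a duration that the definition lacks.

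**Conclusion.** The point holds as a badly fixed definition of a secondary outcome that should be corrected. That rests on the text alone: the protocol requires a sustained run for pain and one rating for disability, so the disability outcome measures time to the first good rating and its results cannot be compared with those for pain.

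The numerical size is not established. Under independent daily ratings and assumed q of 0.05 to 0.20, 30% to 79% of purely fluctuating participants would be counted as recovered by day 7 and 76% to 99.8% by day 28, against under 0.1% for a run of eight. The true figures depend on fluctuation, correlation and rating frequency, none of which the article gives. A reader should not infer that the primary outcome is compromised: its definition, its analysis and the sample size of 182 do not depend on this rule.

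**What to change.** 1. Define disability recovery as the no-interference category held for the same run of consecutive days as the pain endpoint, dated to the first day of the run. Settle whether that run is 7 or more than 7 days once, for both outcomes.
2. State that the interference item is rated daily in weeks 1 to 4.
3. State how recoveries first seen after week 4 are handled: either treat them as interval-censored between contacts, or censor at the end of daily recording, noting that with a run of 8 the latest start that can be confirmed is day 21.
4. Ask the single interference item at the existing assessment just before randomisation. Limit the at-risk set for this outcome to participants with some interference there, and report the number excluded by arm. Exclude no one on a rating made after randomisation.

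**Cost.** Revised wording, one added baseline item, and a daily diary item if it is not already daily. Events will be fewer and later, and dating after week 4 less precise.
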